4.2 Treatment (Manual acupuncture group)

4.2.1 Acupuncture preparation

(1) Disposable, sterile, acupuncture needles (0.30 × 25 mm, 0.30 × 40 mm, Suzhou Tianxie Medical Supplies Co., Ltd., Suzhou, China); (2) Acupuncture device with a longitudinal opening at the bottom (Guangzhou Suixin Medical Supplies Co., Ltd., Guangzhou, China).

4.2.2 Acupoints selection

All acupoints are selected based on traditional Chinese medicine theory and previous articles on PD and constipation(Li et al., 2019; Nazarova et al., 2022), and they are taken bilaterally and positioned in accordance with the National Standard of the People's Republic of China (GB/T12346-2006).

Acupoints: Sishenzhen (four acupoints, consisting of GV 21, GV19, and next to GV20 1.5 cun bilateral), GV24 (Shenting), GV29 (Yintang), ST25 (Tianshu), CV4 (Guanyuan), and ST37 (Shangjuxu).

4.2.3 Operation method

The operation method will be referred to in the textbook Acupuncture and Moxibustion, edited by Wang Fuchun in 2021. The depth of acupuncture will be referred to in the textbook Meridian and Acupoints, edited by Shen Xueyong in 2021.

The patients will be placed in a supine position and wear an eye patch. The physicians will precisely locate the acupoints according to the standard, routinely disinfect the skin of the patients, paste the acupuncture device, adjust the cannula according to the application site, and take the needles to puncture the skin quickly and painlessly.

Table S3 displays acupoints with their insertion depth and direction. All acupoints will be left in place for 30 minutes before being removed, and the needle holes will be pressed for a few moments with a sterilized dry cotton swab when the needles are out. All patients will receive 12 sessions of treatment, three times a week (Tuesday, Thursday, and Saturday), for a period of four weeks.

**Table S3 Acupoints details**

| **Acupoints** | **Location** | **Direction and depth of insertion** |
| --- | --- | --- |
| Sishenzhen  (Four acupoints, consisting of GV21, GV19, and next to GV20 1.5 cun bilateral) | Four points at the vertex of the scalp, grouped around DU20 and located 1.5 cun anterior, posterior, and lateral to it. | Oblique/  0.5 to 0.8 cun |
| Shenting (GV24) | 0.5 cun directly above the midpoint of the anterior hairline. | Oblique/  0.5 to 0.8 cun |
| Yintang (GV29) | On the forehead, at the midpoint between the two medial ends of the eyebrow. | Oblique/  0.5 to 0.8 cun |
| Tianshu (ST25) | 2 cun lateral to the centre of the umbilicus. | Perpendicular/  1 to 1.3 cun |
| Guanyuan (CV04) | 3 cun below the umbilicus. | Perpendicular/  1 to 1.3 cun |
| Shangjuxu (ST37) | 6 cun below Dubi (ST35), one finger-breadth lateral to the anterior border of the tibia. | Perpendicular/  1 to 1.3 cun |

1 cun (≈25 mm) is defined as the width of the interphalangeal joint of the patient's thumb

4.3 Control group (Sham acupuncture group)

4.3.1 Acupuncture preparation

(1) Sterile flat-head acupuncture needles (0.30 mm×10 mm, Guangzhou Suixin Medical Supplies Co., Ltd., Guangzhou, China); (2) Sham acupuncture devices without an aperture (Guangzhou Suixin Medical Equipment Co., Ltd., Guangzhou, China).

4.3.2 Acupoints selection

The acupoints will be the same as in the MA group.

4.3.3 Operation method

The patients will be placed in a supine position and wear an eye patch. The physicians will precisely locate the acupoints according to the standard, routinely disinfect the skin of the patients, paste the sham acupuncture device, adjust the cannula according to the application site, and use the flat-head acupuncture needles without piercing the skin. All acupoints will be left in place for 30 minutes before being removed, and the needle holes will be pressed for a few moments with a sterilized, dry cotton swab when the needles are out. All patients will receive 12 sessions of treatment, three times a week (Tuesday, Thursday, and Saturday), for a period of four weeks.

4.4 Emergency treatment

When patients don`t have bowel movements for more than three consecutive days or experience intolerable symptoms such as bloating due to constipation, they are allowed to use emergency medications under medical supervision with detailed documentation. The emergency treatment consisted of lactulose and glycerin enemas. Lactulose will be used for patients who do not have bowel movements, and glycerin enemas will be used for patients who strain during defecation. The specifications of the emergency medications are as follows: Lactulose Oral Liquid (Hunan Keren Pharmaceutical Company, Approval No.: State Pharmaceutical Code H20093523), 15 ml per dose at 12-hour intervals, 2 doses in total; Glycerin Enemas (Guangdong Hengjian Pharmaceutical Company, Approval No.: H44023815), 1 stick each time in total.

5. Statistical analysis and processing

SPSS 26.0 will be used as the statistical analysis software for this study. We used the intention-to-treat (ITT) principle, regardless of whether the patients completed all assigned intervention sessions. Continuous variables were expressed as mean (SD) or median (IQR); independent t-tests were used for normally distributed values, and Mann-Whitney U tests were used for skewed data. Categorical variables were expressed as frequencies and percentages and analyzed using the χ2 or Fisher exact test, as appropriate. A repeated measures analysis of variance (ANOVA) was used to detect trends in score changes and treatment effects at different time points within groups. Multiple interpolation (MI) methods were used to estimate missing data for the primary and secondary outcomes. To assess the robustness of MI methods under the assumption of randomization, sensitivity analyses of the primary outcome were performed using per-protocol (PP) sets. Differences between groups were reported using 95% confidence intervals and bilateral P values, with values less than 0.05 considered significant.

Safety analysis: Adverse events are analyzed in all participants who received treatment, including the incidence of adverse events and the specific description of adverse events. The data are summarized as n (%). χ2 test or Fisher’s exact test is used for the comparison between treatment groups.

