2.4.1.1 Pilot study and Sample size

We conducted a pilot study to determine the sample size for the randomized controlled trial. Twenty-eight patients were chosen to receive either manual or sham acupuncture (14 patients in each group). We used the change in weekly complete spontaneous bowel movements (CSBMs) from baseline to the end of the trial as an evaluation. Patients who received MA had a mean CSBMs score of 0.964 (standard deviation [SD],1.726), whereas patients who received SA had a score of -0.321. (SD, 1.310). According to PASS version 15.0, 31 patients are needed for each group at a two-sided significance level of 5% and a power of 90%. The sample size estimation was shown in Supplementary Figure S1. With an estimated loss-to-follow-up rate of 20%, we will plan to enroll a total of 78 patients with 39 patients per group.

[figure not shown]

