**Supplementary Figure S3. Trial flow chart**

**Table S1. Time of visit and data collection**

|  | **Baseline** | **Allocation** | **Treatment** | | | | | **Follow-up** | |
| --- | --- | --- | --- | --- | --- | --- | --- | --- | --- |
| Time point (Week) | -1 | 0 | 1 | 2 | | 3 | 4 | 8 |  |
| **Enrollment** |  | | | |  |  |  |  |  |
| Signing consent | **×** |  |  |  | |  |  |  |  |
| Screening | **×** |  |  |  | |  |  |  |  |
| Dose of levodopa | **×** |  |  |  | |  |  |  |  |
| Randomization |  | **×** |  |  | |  |  |  |  |
| **Interventions** |  | | | |  |  |  |  |  |
| Manual acupuncture group |  |  | **×** | **×** | | **×** | **×** |  |  |
| Sham acupuncture group |  |  | **×** | **×** | | **×** | **×** |  |  |
| **Assessments** |  | | | |  |  |  |  |  |
| Weekly CSBMs | **×** | **×** | **×** | **×** | | **×** | **×** | **×** |  |
| CSEAS |  | **×** |  |  | |  | **×** | **×** |  |
| PAC-QOL |  | **×** |  |  | |  | **×** | **×** |  |
| UPDRS |  | **×** |  |  | |  | **×** | **×** |  |
| Assessment of blinding |  | **×** |  |  | |  |  | **×** |  |
| Adverse events |  |  | **×** | **×** | | **×** | **×** |  |  |

Weekly CSBMs= weekly complete spontaneous bowel movements; CSEAS=Constipation Symptom and Efficacy Assessment Scale; PAC-QOL= Patient-Assessment of Constipation Quality of Life questionnaire; UPDRS= Unified Parkinson’s Disease Rating Scale.

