2.4.5 Outcomes Measurements

2.4.5.1 Primary Outcome

**2.4.5.1.1** **The change of weekly complete spontaneous bowel movements (CSBMs).**

We use weekly CSBMs to observe changes in the number of bowel movements in patients with constipation. CSBMs are defined as the number of bowel movements that have occurred in the past 24 hours without the use of emergency medication. CSBMs are recorded by patients on an electronic bowel diary under the direction of an independent outcome assessor. Weekly CSBMs will be collected at baseline (week 0), post-treatment (week 4), and follow-up (week 8), and differences from baseline levels are compared at weeks 4 and 8.

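### The primary comparison is not fixed to one test or effect measure and does not use baseline CSBMs as a covariate, so efficiency and pre-specification are lost, though validity is not

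*Protocol*

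**What the plan says.** **Between-group test.** Section 5 of the protocol gives one rule for all continuous variables: "independent t-tests were used for normally distributed values, and Mann-Whitney U tests were used for skewed data". It states no criterion for normality, no covariate and no separate model for the primary outcome. The same section says that between-group differences will be reported with 95% confidence intervals and two-sided P values.

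**Longitudinal analysis.** The only longitudinal method is a repeated-measures ANOVA, "used to detect trends in score changes and treatment effects at different time points within groups".

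**Missing data.** "Multiple interpolation (MI) methods were used to estimate missing data for the primary and secondary outcomes".

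**Primary outcome.** Section 2.4.5.1.1 defines it on change: "differences from baseline levels are compared at weeks 4 and 8". Section 2.4.1.1 sizes the trial on the same scale: "We used the change in weekly complete spontaneous bowel movements (CSBMs) from baseline to the end of the trial as an evaluation".

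**Baseline.** Section 2.4.5.1.1 puts baseline at week 0. Table S1 labels the week -1 column as baseline and week 0 as allocation, and marks weekly CSBMs in both columns.

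**The concern.** Four features of the stated method deserve attention.

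1. **The test and effect measure are not fixed.** A t-test addresses a difference in means; Mann-Whitney does not. The sample size is built on a difference in mean change. CSBM changes are small counts, so the skewed branch may well be reached, and the quantity reported for the primary outcome would then be settled only once the data are seen.
2. **The rank branch does not fit the imputation plan.** Pooling over imputed data sets needs an estimate and a standard error from each one. Mann-Whitney as named supplies neither, and section 5 does not say what would be pooled.
3. **Baseline is not a covariate.** Subtracting baseline amounts to fixing its regression slope at 1. ANCOVA estimates the slope instead, which generally reduces the variance of the treatment difference and deals better with chance imbalance. This trial has 78 patients and describes no stratification on baseline CSBMs.
4. **A within-group change is called a treatment effect.** Patients are enrolled because they are constipated, so change within one arm mixes any treatment effect with regression to the mean and non-specific response. The objective in section 2.3 is to compare manual with sham acupuncture.

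**Working it through.** **Inputs from section 2.4.1.1.** Mean change 0.964 (SD 1.726) with manual and -0.321 (SD 1.310) with sham acupuncture, 14 patients each; two-sided 5% level; 90% power; 31 per group; 20% loss; 39 per group enrolled.

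**Assumptions (not in the protocol).** The correlation r between baseline and follow-up CSBMs, taken as 0.3, 0.5 and 0.7; and k = baseline SD / follow-up SD, taken as 1, 0.75 and 0.5.

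**Step 1: reproduce the plan's figure.**
- Difference: 0.964 - (-0.321) = 1.285.
- Pooled SD: √((1.726² + 1.310²)/2) = √2.3476 = 1.532.
- Standardised effect: 1.285/1.532 = 0.839.
- Noncentral t, 2n - 2 degrees of freedom: power is 89.1% at n = 30 and 90.1% at n = 31.
- Loss: 31/0.80 = 38.75, so 39 per group and 78 in total.

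The stated sample size is therefore that of an unadjusted t-test on change scores, and it is correct.

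**Step 2: variance with baseline as a covariate.** With follow-up variance s², the change score has variance s²(1 + k² - 2rk), and ANCOVA has residual variance s²(1 - r²). The ratio is

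(1 - r²)/(1 + k² - 2rk),

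which reduces to (1 + r)/2 when k = 1.

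**Step 3: power at 31 per group.** Hold the difference at 1.285 and the change-score SD at 1.532, multiply that variance by the ratio, and use 2n - 3 = 59 degrees of freedom.

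| k | r = 0.3: ratio, power | r = 0.5: ratio, power | r = 0.7: ratio, power |
|---|---|---|---|
| 1 | 0.65, 98.1% | 0.75, 96.3% | 0.85, 94.1% |
| 0.75 | 0.82, 94.9% | 0.92, 92.2% | 0.995, 90.2% |
| 0.5 | 0.96, 91.3% | 1.00, 90.1% | 0.93, 92.1% |

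The gain vanishes where k = r, because the best slope is then exactly 1 and the change score is already optimal. With k = 1, the 95% CI half-width falls from 0.78 to between 0.63 (r = 0.3) and 0.72 (r = 0.7) CSBMs per week.

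**Step 4: does choosing the test from the data distort the error rate?** In 10,000 simulated null trials at 39 per group, the choice was made by a Shapiro-Wilk pretest in each group (an assumed rule, since section 5 gives none). Type I error was 4.9% with normal data and 5.0% with differences of Poisson counts.

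**Step 5: which week is baseline?** Section 2.4.5.1.1 uses week 0, while Table S1 gives the label to week -1. The pilot figures bear on this a little. The means correspond to sums of 13.5 and -4.5 over 14 patients (13.5/14 = 0.964; -4.5/14 = -0.321). Whole-number sums miss them: 13/14 = 0.929 and 14/14 = 1.000; -4/14 = -0.286 and -5/14 = -0.357. Sums of squares of 51.75 and 23.75 return the stated SDs: √((51.75 - 13.5²/14)/13) = 1.726 and √((23.75 - 4.5²/14)/13) = 1.310. If all 14 per group were analysed as observed, the pilot variable was not a difference of two single-week counts.

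**The case against.** The strongest reply is that an unadjusted change-score comparison in a randomised trial is valid, that the planned power reproduces, and that the rule linking distribution to test is stated in advance. The operational normality criterion is detail that a statistical analysis plan could supply. All of this stands.

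Several stronger readings are tempting but are not supported.

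- *Baseline CSBMs are ignored.* They are not: sections 2.4.1.1 and 2.4.5.1.1 both work on change, so baseline enters by subtraction, and change scores respond to imbalance, though not optimally. What is missing is its use as a covariate.
- *Choosing the test from the data inflates false positives.* The simulation shows no material inflation.
- *The plan promises a mean difference that Mann-Whitney cannot supply.* Section 5 promises between-group differences with confidence intervals, without the word mean. A Hodges-Lehmann shift with an interval could accompany the rank test, but section 5 does not name one or say how it would be pooled.
- *The within-group ANOVA is the primary analysis.* Section 5 does not call it primary and also reports between-group differences. The fault is in describing its result as a treatment effect.
- *ANCOVA surely brings a large gain.* That needs similar SDs at baseline and follow-up. Constipated patients recruited near the floor may vary less at baseline, and the gain can then be nil.
- *The pilot proves that baseline was averaged over more than one week.* The half-unit sums suggest this, but imputed pilot values could also give them.

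**Conclusion.** The point holds as a loss of efficiency and pre-specification. Section 5 leaves the primary test and effect measure to the observed distribution, offers a rank branch that does not connect to its own imputation plan, leaves baseline out as a covariate, and words its only longitudinal model as a within-group treatment effect. The sample size is right, and the planned analysis keeps 90% power.

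The size of the gain rests on assumed values. For r from 0.3 to 0.7, power at 31 per group rises from 90.1% to between 94% and 98% with equal SDs. It lies between about 90% and 95% if the baseline SD is 0.5 to 0.75 of the follow-up SD. Over this grid, adjustment costs essentially nothing in power and often gains. The need to fix one test and one effect measure does not depend on r or k. The baseline label is a smaller inconsistency, to be reconciled.

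**What to change.** 1. Name one primary between-group analysis: ANCOVA of weekly CSBMs (or their change; the adjusted difference is the same) on group with baseline CSBMs as covariate, fitted in each imputed data set and pooled. Alternatively, name a linear mixed model with group, week, group-by-week and baseline.
2. Report the adjusted between-group difference with its 95% CI as the effect measure.
3. Use the same form for CSEAS, PAC-QOL and UPDRS.
4. Keep Mann-Whitney as a sensitivity analysis only.
5. Reword the repeated-measures sentence so that claims of treatment effect rest on between-group contrasts only.
6. Reconcile the baseline label in Table S1 (week -1) with section 2.4.5.1.1 (week 0). The week -1 count can be an additional covariate without redefining the endpoint. Averaging weeks -1 and 0 would change the endpoint that section 2.4.5.1.1 fixes, so it is not a free choice.

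The cost is wording in section 5 and Table S1, with no new data and no change in sample size. A mixed model that uses weeks 1 to 3 would draw on counts scheduled in Table S1 but not listed in section 2.4.5.1.1, so that section would need to mention them.

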2.4.3.3 Shedding and rejection criteria

A case is considered to be shed if any of the following criteria are met.

(1) Refusal to cooperate with the study arrangements for personal reasons and no longer suitable to continue the study after assessment.

(2) Sudden onset of serious illness, who is assessed to be unfit to continue with the study.

(3) The occurrence of a serious adverse event or an unexpected event.

(4) Those who withdraw from the study on their own.

A case is considered to be rejected if the following conditions are met.

(1) Those who have not completed treatment as required by this study, or the dose or dosing regimen of the anti-Parkinsonian drug need to be adjusted during treatment.

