4.1 Basic treatment of Parkinson's disease

Both groups will be given basic treatment for PD. Throughout the study, patients in both the MA and SA groups will be required to maintain effective therapeutic doses of anti-Parkinson's drugs at levels like their baseline. Patients with any dosage adjustment, whether an increase, decrease, or adjustment, will be dropped.

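### The per-protocol analysis is named as the check on multiple imputation, but it changes the population and leaves the assumption about the missing outcomes untouched

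*Protocol*

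**What the plan says.** Section 5 (Statistical analysis and processing) sets the analysis population: "We used the intention-to-treat (ITT) principle, regardless of whether the patients completed all assigned intervention sessions". It then deals with missing data: "Multiple interpolation (MI) methods were used to estimate missing data for the primary and secondary outcomes". The wording and the abbreviation point to multiple imputation. The next sentence gives the check: "To assess the robustness of MI methods under the assumption of randomization, sensitivity analyses of the primary outcome were performed", and names the PP sets as the population for it.

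Section 5 does not define the PP set. The nearest text is section 2.4.3.3. Shed cases there include "Those who withdraw from the study on their own", and rejected cases are "Those who have not completed treatment as required by this study, or the dose or dosing regimen of the anti-Parkinsonian drug need to be adjusted". Section 4.1 adds: "Patients with any dosage adjustment, whether an increase, decrease, or adjustment, will be dropped".

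Section 2.4.1.1 plans for 20% loss to follow-up, with 39 patients enrolled per group to keep 31. Section 5 ends with an analysis of dropouts: their causes, their proportion, and a comparison between the groups.

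**The concern.** Standard multiple imputation assumes that, given the observed data, patients with missing outcomes resemble those with observed outcomes. The data cannot confirm this. Robustness is shown by changing what is assumed about the unobserved values, in the same randomised population, and seeing whether the conclusion survives.

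A PP analysis does something else. It removes patients according to what happened after randomisation and uses no information about the outcomes that were not seen. Treating the remaining patients as representative is an assumption at least as strong as missing at random, with post-randomisation selection added.

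At stake is how the primary result is read. If acupuncture patients leave because the treatment is not helping, both analyses can overstate the effect by a similar amount, and their agreement could be taken as reassurance that it does not provide.

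**Working it through.** **Inputs from section 2.4.1.1.** Pilot mean change in weekly complete spontaneous bowel movements (CSBMs): 0.964 (SD 1.726) with acupuncture and -0.321 (SD 1.310) with sham. Two-sided 5% level, 90% power, 31 per group, 20% loss, 39 per group, 78 in total.

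**The plan's own figures reproduce.**
- Difference: 0.964 - (-0.321) = 1.285.
- Pooled SD: sqrt((1.726² + 1.310²)/2) = 1.532.
- The normal approximation gives 30 per group. The noncentral t calculation with unequal variances gives 89.1% power at 30 and 90.06% at 31, hence 31.
- Loss: 31/0.8 = 38.75, rounded up to 39 per group, 78 in total.

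The sample size is not affected by this point.

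**Effect of a departure from missing at random.** Assumed, not in the protocol: 20% missing in each group (about 8 of 39); missing acupuncture patients in truth worse by k CSBMs per week than imputation supposes; missing sham patients imputed correctly.
- Overstatement of the difference = missing fraction × k.
- If missing acupuncture patients did as the sham group, k = 1.285 and the overstatement is 0.20 × 1.285 = 0.257, leaving 1.285 - 0.257 = 1.028.
- SE with 31 observed per group: sqrt(1.726²/31 + 1.310²/31) = 0.389. Holding it fixed, 1.028/0.389 = 2.64, still significant.
- Significance is lost when 1.285 - (8/39) × k = 1.96 × 0.389, that is at k of about 2.5 CSBMs per week.

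**Would the named check show it?** A simulation used 600 trials per scenario, 39 per group, 20% missing, 10 imputations, and a covariate correlated 0.3 with the outcome (assumed). The PP set was represented by patients with observed outcomes.

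| k | True difference, all randomised | Multiple imputation | Missing patients left out |
| --- | --- | --- | --- |
| 0 | 1.30 | 1.30 | 1.30 |
| 1 | 1.09 | 1.28 | 1.28 |
| 2 | 0.85 | 1.25 | 1.25 |
| 3 | 0.69 | 1.29 | 1.29 |

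The small movements in the last two columns are simulation error. The two estimates correlated at about 0.97 to 0.98. In this setting they agree when missing at random is true and agree equally well when it is badly wrong.

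**The case against.** Several points on the other side are fair.

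- **The sentence may claim less.** It speaks of robustness under an assumption and does not say that the assumption itself is tested. Comparing imputed with non-imputed results shows whether the imputed values drive the answer, which is a limited but real question. This stands as a reading. PP still does not answer it cleanly, because it changes the population as well as the handling of missing data.
- **A reader might infer that PP drops exactly the patients with missing outcomes.** The protocol does not support that. The shed and rejected categories are never tied to the PP set. A patient who finished treatment and missed only week 8 could stay in. A patient with a dose change might leave with outcomes observed, or might already be missing after being dropped. Incomplete overlap makes a difference between the two analyses harder to interpret.
- **The diary may carry the information.** Table S1 schedules weekly CSBMs in weeks 1 to 4. If failure shows there before withdrawal and those weeks enter the imputation model, missing at random becomes more credible, and imputation and PP could differ. That would strengthen the imputation. It would not make PP a test of it, since any difference would mix two changes.
- **Dropouts are examined elsewhere.** Section 5 compares them between groups with causes. That bears on whether losses are differential, but it is descriptive and does not vary the missing values.
- **The SAP may add analyses.** It may. The point concerns the role the protocol gives to PP, not an omission.

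**Conclusion.** The point holds as a misassigned analysis. PP is a reasonable supplementary analysis but cannot serve as the check on multiple imputation. Agreement would be expected even if missing acupuncture patients did worse, and disagreement would confound population with missing-data handling. This rests on reading the stated assumption as missing at random, and on PP excluding most patients with missing outcomes. Both are inferences, though PP would be the wrong tool even if the overlap were partial.

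The overstatement of about 0.26 is an illustration, not an estimate. It is 20% of the planned effect only because the shortfall was set equal to that effect and 20% were assumed missing. A similar imputation error in the sham group would offset it.

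Two stronger inferences are not supported. One is that the primary result would probably be overturned: that needs a shortfall of about 2.5 CSBMs per week, nearly twice the planned effect. The other is that the protocol has a rule declaring the result robust if PP agrees: section 5 contains none.

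**What to change.** In section 5, describe the PP analysis as supplementary and concerned with adherence, and remove its role as the check on imputation. Name instead, for the primary outcome, one analysis in all randomised patients that varies the missing values. Either of these is enough:

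- a delta-adjusted tipping-point analysis, lowering the imputed acupuncture-group values in steps until significance is lost; or
- imputation of missing acupuncture-group outcomes from the sham-group distribution.

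Possible wording: *The sensitivity of the primary result to the missing-at-random assumption will be assessed in all randomised patients by progressively lowering the imputed acupuncture-group values and reporting the shift at which significance is lost. The per-protocol analysis is supplementary.*

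The imputation model and the step sizes can stay in the SAP. The cost is a few more analysis runs, with no change to sample size or data collection. The reported robustness may look less favourable.
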